# Immediate versus delayed loading of strategic mini dental implants for the stabilization of partial removable dental prostheses: a patient cluster randomized, parallel-group 3-year trial

**DOI:** 10.1186/s12903-016-0259-z

**Published:** 2016-07-30

**Keywords:** Mini dental implant, Strategic implant, Partial removable dental prosthesis, Supplementary abutment, Implant therapy

## Abstract

**Background:**

Acceptable short-term survival rates (>90 %) of mini-implants (diameter < 3.0 mm) are only documented for mandibular overdentures. Sound data for mini-implants as strategic abutments for a better retention of partial removable dental prosthesis (PRDP) are not available.

**Methods/design:**

The purpose of this study is to test the hypothesis that immediately loaded mini-implants show more bone loss and less success than strategic mini-implants with delayed loading. In this four-center (one university hospital, three dental practices in Germany), parallel-group, controlled clinical trial, which is cluster randomized on patient level, a total of 80 partially edentulous patients with unfavourable number and distribution of remaining abutment teeth in at least one jaw will receive supplementary min-implants to stabilize their PRDP. The mini-implant are either immediately loaded after implant placement (test group) or delayed after four months (control group). Follow-up of the patients will be performed for 36 months. The primary outcome is the radiographic bone level changes at implants. The secondary outcome is the implant success as a composite variable. Tertiary outcomes include clinical, subjective (quality of life, satisfaction, chewing ability) and dental or technical complications.

**Discussion:**

Strategic implants under an existing PRDP are only documented for standard-diameter implants. Mini-implants could be a minimal invasive and low cost solution for this treatment modality.

**Trial registration:**

The trial is registered at Deutsches Register Klinischer Studien (German register of clinical trials) under DRKS-ID: DRKS00007589 (www.germanctr.de) on January 13^th^, 2015.

**Electronic supplementary material:**

The online version of this article (doi:10.1186/s12903-016-0259-z) contains supplementary material, which is available to authorized users.

## Background

In the USA and many European countries there is a decline in edentulism in all age groups. However, the number of partially edentulous patients will increase with a shift in older age groups because the populations of industrial nations are growing older [1, 2]. In Germany, most individuals with reduced dentition demand and receive partial removable dental prostheses (PRDP) that are either retained by double crowns, clasps, ball- or other attachments [3]. The longevity of the remaining teeth and the PRDP depends on the number and localization of the abutments as shown in studies that analysed double crown retained prostheses [4]. According to epidemiological studies, the lower the number of remaining teeth the higher is the incidence of further tooth loss [5]. From the clinical point of view, symmetrical support by the abutment teeth is suggested regardless of the attachment system used [6]. Supplementary implants in strategic positions can ensure a change from a critical prosthetic support (unilateral, linear) to a more favourable support configuration [6–8]. The retention and the stability of PRDPs are better if both quadrants of the jaw show abutments on strategically important areas such as the canine and posterior teeth [9]. This may protect the remaining teeth from overload and reduce possible rotational movements of the RPDP [9]. When an incisor is the terminal abutment in the quadrant, distal implants can reduce the use of retentive elements such as clasps, which provides better aesthetics and periodontal stability [8–10].

For the combination of teeth and implants to support RPDPs, either double crowns [7, 8, 11, 12] or resilient ball-attachments [6, 10, 13–19] were used on standard-diameter implants (>3.5 mm).

Standard-diameter implants require a sufficient width of the alveolar ridge (>5.5 mm). Otherwise, bone augmentation procedures are indicated, which would increase the risk of possible side effects and increase costs and treatment duration [20].

Mini-implants (diameter < 3.0 mm) are suggested to be a prosthodontic alternative to standard-diameter implants for solutions in patients with narrow alveolar ridges [20–25]. Additional advantages of mini-implants are the simplified treatment procedures with a flat learning curve, low cost, and the possible flapless surgical procedure which can decrease the post-surgical morbidity [20]. With one exception [26], mini-implants used for the retention of removable prostheses are usually one piece with a retentive ball-attachment. Therefore, no-load osseointegration is not achievable. The female matrices (housings with plastic O-rings) can be immediately polymerised into the prostheses after placement of implants with sufficient primary stability. Mini-implants are mainly used for the stabilization of complete dentures. However, long-term survival data for mini-implants are lacking and acceptable short-term survival rates (>90 %) of mini-implants are only documented for mandibular overdentures [20, 27, 28]. The short-term survival rates of immediate loaded mini-implants that are used to stabilize maxillary overdentures were unacceptably low and ranged between 54 % and 85 % [21–23]. The mean radiographic bone loss was >5 mm in the first year and therefore higher than in studies on mandibular overdentures with mean bone loss rates between 0.4 and 1.2 mm [24, 28]. In a multi-center study [25], the 4-year survival rate of mini-implants for complete denture stabilization was about 95 % without significant differences between the maxilla and mandible. In that study, all MDIs in the receiving jaw were immediately restored by rebasing the dentures with a soft liner when the insertion torque of one MDI was < 35 Ncm. The housings were picked-up after 3–4 months. The mean bone loss was insignificantly higher in the maxilla (0.8 mm) than in the mandible (0.5 mm) [29]. In another study on mini-implant supported mandibular overdentures, delayed loading appeared to be preferable to immediate loading regarding implant survival and bone loss [30]. Sound data of mini-implants as strategic abutments for a better retention of PRDPs are not available [20, 23, 27].

## Methods/design

### Study aim and design

The objectives of this study are to show that (1) immediately loaded (with housings)/restored (soft relining) mini-implants show more bone loss and less success than delayed loaded strategic mini-implants, (2) strategic mini-implants improve patients’ quality of life, patients’ satisfaction, chewing function, retention of the denture, and periodontal health of remaining abutment teeth. However, the improvements in the immediately loaded group will occur faster than in the delayed loaded group.

The protocol of this multi-center randomized parallel-group clinical trial follows the SPIRIT guidelines [31]. The study was designed according to the Good Clinical Practice guidelines (ICG-GCP) and the principles of the Declaration of Helsinki as revised in 2008.

### Study setting and participants

The Dental School at the Greifswald university hospital and three German private dental practices specializing in dental implantology and prosthodontics participate.

Study participants had to meet the following inclusion criteria:At least 2-months-old double crown-retained or clasp-retained PRDP in the maxilla and/or mandible that shows an unfavourable number and distribution of remaining abutment teeth in at least one quadrant of the study jaw (see classification Table 1).

**Table 1 Tab1:**
[figure not shown]
Classification for strategic mini dental implants on quadrant levelThe abutment teeth need to have healthy periodontal conditions (pocket dephts ≤ 4 mm, no bleeding on probing, attachment loss < two third of the root length, mobility grade ≤ 2).Vital or endodontically treated abutment teeth with a sealed root filling to the apical region without apical periodontitis.No contraindication for implantation, and sufficient bone in the study jaw to place an implant without augmentation proceduresWritten informed consent to participate in the study.

Exclusion criteria for participation wereContraindication for implantation without augmentation caused by local bone deficitsPatients who are satisfied with their PRDPPatients who refuse randomizations to one of the study groupsPoor general health, e.g. Class III-IV according to the classification of the American Society of Anaesthesiology (ASA), severe renal/or liver disease, history of a radiotherapy in the head region, chemotherapy at the time of surgical procedure, non-compensated diabetes mellitus, HIV,Ongoing intravenous bisphosphonate therapyMental disorders (anamnestic)Drug abuse (anamnestic)Active periodontal disease and/or poor oral hygiene (mean plaque index and/or mean sulcus bleeding index ≥ 1)

### Interventions

Dentists of the centers with experience in dental implantology for more than ten years, who are familiar with the mini-implant system, perform the surgical and prosthetic treatment. Standard operating procedures were specified in a manual and imparted during the first calibration meeting. The first implant placement in each center was supervised by the treatment coordinator (TC) of the leading center.

Mini dental implants (MDI, 3 M ESPE, Seefeld, Germany) with lengths of 10 to 18 mm and diameters of 1.8 mm, 2.1, and 2.4 mm are used for the stabilization of PRDPs (Figs. 1 and 2). The total number of abutments per quadrant (with unfavourable distribution and number of remaining abutment teeth) will be increased to at least 3 in the maxilla or at least 2 in the mandible by the insertion of strategic MDIs (Table 1). The posterior MDI should be placed at the most posterior area of the dental arch according to the local bone volume. In the mandible, the MDIs should be located always mesial of the mental foramen. Whenever possible, the region of the canine should be occupied by an MDI (alternatively the regions of the first premolar and the lateral incisor should show abutments after intervention). If the insertion torque of one implant is < 15 Ncm due to poor bone quality the patient must be excluded from the study. Recesses for female matrices (housings) were prepared in the existing PRDP. Thereafter, a sealed envelope with the randomization detail was opened and the patient was allocated either to test group A (immediate loading/restoration) or control group B (delayed loading).

**Fig. 1 Fig1:**
[figure not shown]
Pantomographic image of 4 mandibular strategic mini dental implants

**Fig. 2 Fig2:**
[figure not shown]
Mini dental implants presented in Fig. 1 after two weeks

Test group A (immediate loading/restoration):

If the insertion torque of all MDIs in the study jaw was ≥ 35 Ncm implants were immediately loaded. The female housings were seated on the ball attachments and picked-up using self-cured acrylic resin (Secure hard pick-up kit, 3 M ESPE, Seefeld, Germany). If the insertion torque of one MDI in the study jaw is < 35 Ncm all MDIs of this jaw were immediately restored by relining the dentures with a soft material (Secure soft reline kit, 3 M ESPE, Seefeld, Germany) embracing the ball heads. After 4 months, the soft base were substituted with the housings and acrylic resin (Fig. 3).

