**Fig. 3 Fig3:**
[figure not shown]
Housings for the implants presented in Fig. 2 were picked up after 4 months

Control group B (delayed loading):

The recesses for the female housings in the PRDP remained empty for 4 months. Thereafter, the housings were seated on the ball attachments and picked-up using self-cured acrylic resin (Secure hard pick-up kit, 3 M ESPE, Seefeld, Germany). In the case of mucosal hyperplasia around the implant before to the fourth months, the recesses should be relined earlier using the soft material.

During the study period and thereafter the participants will be treated by the dentists of the study sites according to their dental healthcare needs. Treatments could arise from study-related events, e.g. implant or tooth loss, prosthesis fractures or study-independent events, e. g. in the opposite jaw. Treatments before study closure will be considered as outcomes.

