### Primary outcome: bone level

Because jaw was used for randomization, we extend Gilthorpe’s mixed model by inserting jaw to levels for patient, tooth, and site [38] and adjust for model complexity by using the Kenward-Roger correction [39]. To ensure hierarchical levels, tooth positions within each jaw are coded from 1 to 16 instead of from 1 to 32 on patient level. The first adjustment set consists of risk factors of periodontal disease including age, gender, and smoking [40]; and design variables including centre, jaw [41], jaw classification, and time. Because X-ray at t_0_ is assessed before differentiating treatment in groups, it is a baseline measurement which can additionally be used to increase efficiency [42]. Note also the discussion on pages 158–160 in Harrell’s textbook [43]. The syntax of the basic confirmatory model with the highest statistical power for the factor group is (Stata’s version 14):

Here, only the time points t_4_ and t_6_ are used as dependent variable (Table 2). To interpret changes after 12 and 36 months in exploratory analyses, we include t_0_ as dependent variable:

In sensitivity analyses, we allow for continuous time instead of points in time, for correlated random effects, or for random effects of other than tooth level and suspend the Kenward-Roger correction. In the second adjustment set, jaw classification is replaced by patient’s mean probing depth before randomization; in the third and fourth set, school education will be added to the first and second set, respectively.

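### Arm A is a torque-driven composite of immediate loading and soft reline; adjusting for torque class and adding an exploratory torque-class estimate would let the trial speak to immediate loading itself

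*Protocol article*

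**What the plan says.** **Order of events (Protocol article, Interventions).** The implants are placed and the low-torque rule applies: "If the insertion torque of one implant is < 15 Ncm due to poor bone quality the patient must be excluded from the study". Recesses are prepared in the prosthesis. "Thereafter, a sealed envelope with the randomization detail was opened".

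**Arm A (Test group A).** "If the insertion torque of all MDIs in the study jaw was ≥ 35 Ncm implants were immediately loaded". If one implant falls short of 35 Ncm, "all MDIs of this jaw were immediately restored by relining the dentures with a soft material". For these jaws, "After 4 months, the soft base were substituted with the housings and acrylic resin".

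**Arm B (Control group B).** "The recesses for the female housings in the PRDP remained empty for 4 months". No torque rule applies.

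**Analysis (Randomization and blinding; Primary outcome: bone level; Table 2; Additional notes).** Randomisation is stratified by jaw and centre. "The first adjustment set consists of risk factors of periodontal disease including age, gender, and smoking", together with centre, jaw, jaw classification and time; the bone level at t0 may be added. The second set replaces jaw classification by mean probing depth, and the third and fourth add school education. The planned subgroup is jaw class, and the additional analysis is maxilla versus mandible. Torque is in none of these lists.

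**Wording of the hypothesis.** Study aim and design names a test condition that covers both loading with housings and restoration by soft relining, and the Discussion does the same. The Abstract and Outcomes refer to immediately loaded implants only.

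**The concern.** Two different treatments sit under one arm label, and torque alone chooses between them. The text itself ties very low torque to poor bone quality, so torque is plausibly related to bone loss as well. The plan nevertheless lists its confounders, four adjustment sets and a subgroup without it.

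Interpretation is what is at stake. A reader of the abstract will take the result as an answer about immediate loading. If the pooled difference is small, the planned analyses cannot say whether immediate loading does little harm or whether soft-relined jaws pulled the average down. An unplanned attempt to find out would probably compare loaded with restored jaws inside arm A, or loaded jaws in arm A with all of arm B. Both comparisons are confounded by torque. The comparison that keeps randomisation is A versus B within the same torque class, and it is not prespecified.

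**Working it through.** **1. Is torque class a pre-allocation variable in both arms?** The envelope is opened after the implants are in and the recesses are cut. At insertion the operator does not know the arm. To apply the 15 Ncm exclusion to every patient, and the 35 Ncm rule if arm A is drawn, torque has to be measured at insertion in everyone. Torque class therefore cannot be affected by allocation. The article does not say that the values are written down for arm B.

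**2. The plan's own figure.** Inputs from Sample size: difference 0.9 − 0.5 = 0.4 mm, SD 0.5, two-sided alpha 0.05, 80% power. The standardised effect is 0.4/0.5 = 0.8. The two-sample t-test (noncentral t) gives n = 25.5, rounded up to 26 per group, with power 0.807. The figure reproduces. With 40 allocated per group and 75% response, 40 × 0.75 = 30 are evaluable, with power 0.861. The 0.4 mm is taken from immediately loaded regular-diameter implants (0.91 mm against 0.51 mm at 1 year); no soft-reline component is mentioned.

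**3. Illustration for the pooled contrast.** Let f be the share of arm A that is soft-relined and r the soft-reline effect as a fraction of the loading effect. Both are assumptions.

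- Pooled difference = 0.4 × [(1 − f) + f·r]
- Variance in arm A = 0.25 + f(1 − f) × [0.4(1 − r)]²
- SD used = √[(0.25 + variance in arm A)/2]

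| f | r | Difference (mm) | SD | Power, 30 per arm |
|---|---|---|---|---|
| 0 | – | 0.40 | 0.500 | 0.86 |
| 0.25 | 0 | 0.30 | 0.515 | 0.60 |
| 0.25 | 0.5 | 0.35 | 0.504 | 0.75 |
| 0.50 | 0 | 0.20 | 0.520 | 0.31 |
| 0.50 | 0.5 | 0.30 | 0.505 | 0.62 |

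If r = 1, the difference stays at 0.40 mm for every f.

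**4. What the within-class comparison could deliver.** Assume the same share f below 35 Ncm in both arms, difference 0.4 mm and SD 0.5 in the class at 35 Ncm or more. The number per arm is 30(1 − f), and SE = 0.5 × √(2/n).

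- f = 0.25: n = 22.5, SE = 0.149, power 0.75, 95% CI half-width about 2.02 × 0.149 = 0.30 mm.
- f = 0.50: n = 15, SE = 0.183, power 0.56, half-width about 2.05 × 0.183 = 0.37 mm.

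In the lower class with f = 0.25, n = 7.5, SE = 0.258 and the half-width is about 2.16 × 0.258 = 0.56 mm.

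**5. The interaction term.** Its SE is √(SE² of one class + SE² of the other). For f = 0.25 this is √(0.149² + 0.258²) = 0.298. A full 0.4 mm difference between classes (r = 0) is then 0.4/0.298 = 1.34 standard errors, with power about 0.26. For f = 0.50 the SE is √(2 × 0.183²) = 0.258, the ratio is 1.55 and power is about 0.33. The term can describe a difference between classes but cannot settle whether there is one.

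**The case against.** The strongest reply is that the composite is declared. The study aim, the arm A label and the Discussion all name loading and restoration together. The pooled contrast estimates that strategy without bias, and on this reading there is no dilution, only a different question. **This stands.** A reader might infer that omitting torque biases the A-B comparison; it does not, because torque precedes allocation and is balanced in expectation. Adjustment can add precision only. What the reply leaves open is the narrower hypothesis in the Abstract and Outcomes and the source of the 0.4 mm.

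A reader might also infer that the trial cannot isolate immediate loading. The documents do not support that: the design permits the within-class comparison, and it is simply not planned.

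The power figures can be challenged too. The share f and the ratio r appear nowhere in the documents, and even the direction is open. Soft-relined jaws have lower torque, and the soft material engages the ball heads at once while arm B recesses stay empty. Their excess loss could equal or exceed that of loaded jaws. **This stands**, so step 3 is an illustration and does not measure a defect.

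It can be said that torque class in arm B is unknown, because the 35 Ncm threshold appears only under arm A. This fails for measurement, since the arm is not known at insertion. It holds for recording, which must be confirmed.

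Finally, an analysis plan not shown may contain an exploratory stratum, and the model syntax is missing from the text at hand. The article does, however, list its covariates, adjustment sets and subgroup explicitly, and torque is absent from each list.

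**Conclusion.** The point holds as a cheap improvement. The confirmatory A-B contrast is valid for the composite strategy and should stay. The gap is that part of the document asks about immediate loading only, while the planned analyses do not separate it from soft reline, although a pre-allocation variable that would do so is measured.

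The size cannot be fixed from the documents. With assumed soft-reline shares of 25% to 50% and an effect of none or half in those jaws, the pooled difference would be 0.20 to 0.35 mm and power 0.31 to 0.75 at 30 per arm. With an equal effect nothing is lost. A reader might want to treat the estimate at 35 Ncm or more as the trial's answer. Its power of about 0.56 to 0.75 under the same shares, and the weak interaction test, do not support placing it ahead of the confirmatory contrast.

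**What to change.** Recruitment and implant placement are finished, so the change concerns the analysis plan and should be made before group-level results are seen.

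1. Keep the pooled A-B contrast as the confirmatory estimate. State that it refers to the composite of immediate loading or restoration, and align the hypothesis wording in the Abstract and Outcomes with Study aim and design.
2. Confirm that insertion torque was recorded in both arms.
3. If so, add jaw-level torque class (all mini-implants at 35 Ncm or more, versus any from 15 to below 35 Ncm) as a fixed covariate in the bone-level and implant-success models, in both arms.
4. Prespecify as exploratory the group-by-torque-class term, with the A-B estimate and confidence interval in each class. Also state that comparisons of loaded jaws in arm A with restored jaws in arm A, or with all of arm B, will not be read as effects of loading.

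The cost is one covariate and one interaction (1-2 degrees of freedom) and wide intervals within class. If torque proves unrecorded in arm B, only step 1 remains, and the report should say that immediate loading was not separated from soft reline. No treatment rule changes.

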**Fig. 3 Fig3:**
[figure not shown]
Housings for the implants presented in Fig. 2 were picked up after 4 months

Control group B (delayed loading):

The recesses for the female housings in the PRDP remained empty for 4 months. Thereafter, the housings were seated on the ball attachments and picked-up using self-cured acrylic resin (Secure hard pick-up kit, 3 M ESPE, Seefeld, Germany). In the case of mucosal hyperplasia around the implant before to the fourth months, the recesses should be relined earlier using the soft material.

During the study period and thereafter the participants will be treated by the dentists of the study sites according to their dental healthcare needs. Treatments could arise from study-related events, e.g. implant or tooth loss, prosthesis fractures or study-independent events, e. g. in the opposite jaw. Treatments before study closure will be considered as outcomes.

